#### Secondary outcomes

The secondary outcomes will be the prolonged abstinence rate, the abstinence rate at other time points, the results from a saliva cortisone test, and scores on the Fagerstrom Test for Nicotine Dependence (FTND), the Autonomy over Tobacco Scale (AUTOS), the Hamilton Anxiety Rating Scale (HAM-A), the Self-rating Anxiety Scale (SAS), and the Pittsburgh Sleep Quality Index (PSQI). Additionally, we will conduct safety assessments of and evaluate cost of treatment.

### Detection time point of outcomes

Baseline will be recorded before clinical trial, safety will be conducted at the beginning and end of trial. The clinical symptoms, efficacy observation indicators, laboratory indicators and scale evaluation of the patients were examined before treatment and at the follow-up of 2, 4, 6, 8, 16 and 24 weeks after treatment.

All the above results will be timely and truthfully filled in the clinical case report form (CRF).

### Assessment of adverse events

All adverse events will be reported in detail in an observation table (Table 1), including the type of event, the extent of symptoms or diseases, the date of onset, frequency, duration, the remission date, treatment measures, treatment process, results, and follow-up, for evaluation of any correlations between adverse reactions and A&AA or NRT.

**Table 1 T1:** Description of the study schedule.

**Task**	**Screening**	**Observation period**				**Follow-up period**		**Unplanned follow-up**
	**Visit 0** **Week 0**	**Visit 1** **Week 2**	**Visit 2 Week 4**	**Visit 3** **Week 6**	**Visit 4 Week 8**	**Visit 5** **Week 16**	**Visit 6 Week 24**	
Medical history collection	√	–	–	–	–	–	–	–
Signing informed consent	√	–	–	–	–	–	–	–
Inclusion criteria	√	–	–	–	–	–	–	–
Exclusion criteria	√	–	–	–	–	–	–	–
Basic information	√	–	–	–	–	–	–	–
Vital signs	√	√	√	√	√	√	√	√
Blood and urine tests	√	–	–	–	√	–	√	
Liver and kidney function	√	–	–	–	√	–	√	
Respiratory carbon monoxide determination	√	√	√	√	√	√	√	
Coagulation	√	–	–	–	√	–	√	
Blood lipids + HCY	√	–	–	–	√	–	√	
Saliva cotinine test	√	–	–	–	–	√	√	
ECG	√	–	–	–	–	–	√	
FTND	√	√	√	√	√	√	√	
AUTOS	√	√	√	√	√	√	√	
HAM-A	√	√	√	√	√	√	√	
SAS	√	√	√	√	√	√	√	
PSQI Scale	√	√	√	√	√	√	√	
Adverse event record	–	√	√	√	√	√	√	
Combined medication records	√	√	√	√	√	√	√	
Termination test evaluation	–	√	√	√	√	√	√	

*AUTOS, Autonomy over Tobacco Scale; ECG, electrocardiogram; FTND, Fagerstrom Test for Nicotine Dependence; HAM-A, Hamilton Anxiety Rating Scale; SAS, Self-rating Anxiety Scale; PSQI, Pittsburgh Sleep Quality Index.*

*“√” is recorded when necessary*.

### Assessment of health economics

A cost-effectiveness analysis from a societal perspective will be performed. Cost information, including that regarding medical and non-medical costs, will be collected during treatment, at the end of treatment, and at week 24. The effectiveness index will be considered the primary outcome (Table 1). Cost-effectiveness ratio (CER) and incremental cost-effectiveness ratio (ICER) will be calculated to compare the difference in the cost and clinical outcomes between the two groups. The stability of the results will be tested using sensitivity analysis by the means of bootstrapping and presented with cost-effectiveness acceptability curves (CEAC).

### Data management and monitoring

The data will be monitored by the Electronic Data Capture System (EDC) of the Clinical Research and Data Center of Guangzhou University of Chinese Medicine. Dynamic monitoring of patient enrolment, data entry, and quality verification will be performed by this system in order to strengthen data accuracy and maintain data quality. Study Completed Statistical results will be public access file upload in Chinese Clinical Trial Registry. Participants' personal information will be kept confidential before, during and after the trial.

### Statistical analysis

Data management and statistical analyses for this study will be carried out blingdingly by an independent third party (Clinical Research and Data Center, Guangzhou University of Chinese Medicine). The statistical tests involved in this study will include unilateral and bilateral tests with a significance level of α = 0.05. Statistical analysis will be completed using IBM SPSS 27.0.

All Subjects who will be randomized to undergo at least one treatment comprised the Intention-To-Treat (ITT) population of the study. Subjects who will be randomized into groups and underwent at least one treatment constitute the Safety group of this study. The Per-Protocol analysis data set (PPS), which refers to the cases that comply with the study plan, with the following conditions: the primary variables are clear, no baseline variables are missing, completed all scheduled studies for the 8-week treatment period, and subjects who seriously violate the protocol will be excluded. The safety dataset will be analyzed for subjects who have received at least one treatment after randomization. General demographic, clinical characteristics, and other baseline data will be used to compare the balance between the two groups. Primary outcome measures will be analyzed using ITT population, secondary outcome measures and other outcomes will be analyzed using PPS population. The safety analysis will use the safety population.At each time point, descriptive analyses will be performed to show the two groups of different means (SD and 95% CI) and the rate of outcome change. If the data follow normal distribution, the independent sample *T*-test will be used for comparison. If not, the rank sum test is applied. In order to distinguish therapeutic effects from temporal effects, analysis will be performed using a repeated measurement design.

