### Sample size

According to a previous randomized, controlled study of acupuncture for smoking cessation (15), we expect that the success rates for smoking cessation will be on average 44% in the NRT (control) group and 60% in the A&AA (treatment) group, using the abstinence rate for smoking cessation at week 24 (24-h carbon monoxide [CO] clearance rate of <10 parts per million) as the primary outcome. Using PASS 2008 software, the sample size required for each group was estimated to be 152 cases by two independent sample rate comparison methods.

Therefore, considering an expected loss of 15% during the follow-up period, we will recruit a total of 360 (≈304/0.85) volunteers for this study. Allocation into the two groups will be assigned in a 1:1 ratio, and each group size will be set at 180.

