## Discussion

At present, most RCTs on acupuncture for smoking cessation usually use blank controls or fake acupuncture for comparison (22). These studies cannot directly and objectively show the effect of acupuncture on smoking cessation. In 2015, the clinical guideline for Smoking cessation in China (23) recommended three drug therapies: NRT, bupropion, and varenicline. To objectively prove if A&AA can aid successful quitting of smoking, it is necessary to compare it with the drug treatments described in the clinical guidelines. In Jang et al.'s clinical study on smoking cessation, the control group received only NRT and counseling, and the trial group received Traditional Chinese Medicine (TCM). The study found that the effect of smoking cessation was improved using TCM, but the increase of TCM treatment cost had no statistical significance on whether TCM could improve the success rate of smoking cessation (24). Our study design is different in that we compared A&AA and NRT to verify if acupuncture is superior to NRT for smoking cessation. Acupuncture may have greater safety, fewer side effects, while being cost-effective. In China, hospitals at all levels set up acupuncture or TCM clinics, and people who want to quit smoking can easily find A&AA intervention. However, psychological counseling and smoking cessation medicine are not widely available, and it is difficult for people to avail these services.

This study will investigate the effectiveness, safety, and economic benefits of the use of A&AA for smoking cessation. This protocol is designed to be a prospective, parallel, multicentre, large-scale, randomized controlled clinical trial. In this trial, Nicotine patches will be provided to the control group as a form of NRT, since all licensed forms of NRT (gum, transdermal patch, nasal spray, inhalator, and sublingual tablets/lozenges) have been reported to help people increase their chances of successfully stopping smoking and to reduce nicotine withdrawal symptoms.

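### One-sided and two-sided tests are both allowed at α = 0.05, and neither is assigned to the primary week-24 superiority comparison

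*Protocol article*

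**What the plan says.** The Statistical analysis section sets one rule for all tests: "The statistical tests involved in this study will include unilateral and bilateral tests with a significance level of α = 0.05". It does not list which tests are one-sided and which are two-sided. The Primary outcome and Secondary outcomes sections do not do so either, nor does the Safety analysis section, which names the tests for adverse events.

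The Discussion gives the aim a direction. The trial is meant "to verify if acupuncture is superior to NRT for smoking cessation".

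The Sample size section assumes "44% in the NRT (control) group and 60% in the A&AA (treatment) group" and reports that "the sample size required for each group was estimated to be 152 cases". It then allows for 15% loss and sets 360 in total, 180 per group. It gives no alpha, sidedness or power.

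Confidence intervals are at the 95% level wherever the article mentions them, in Statistical analysis and in Handling of missing data.

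**The concern.** For a claim of benefit, a one-sided test at 0.05 is as lenient as a two-sided test at 0.10. A rule that admits both at the same nominal 0.05 therefore admits two different error rates for the same claim. The aim is directional and no non-inferiority margin is stated, so the superiority comparison is a natural place for a one-sided test to be used.

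The main conclusion is at stake. A difference that lies between the two critical values is significant under one permitted test and not under the other. A reader of the results could not tell from this article which test was planned. A one-sided test for benefit also could not conclude that A&AA is worse than NRT.

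**Working it through.** **Inputs.** From Sample size: p₁ = 0.44 (NRT), p₂ = 0.60 (A&AA), 152 per group before loss, 15% loss, 180 per group recruited. From Statistical analysis: α = 0.05, sidedness open. Power is not stated, so 80% is an assumption and 80% to 90% is examined. The difference is d = 0.16, and the pooled rate is p̄ = (0.44 + 0.60)/2 = 0.52.

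**Reproducing the 152.** Pooled two-proportion formula without continuity correction:

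n = [z_α·√(2p̄(1−p̄)) + z_β·√(p₁(1−p₁) + p₂(1−p₂))]² / d²

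Here √(2 × 0.52 × 0.48) = 0.7065 and √(0.2464 + 0.2400) = 0.6974.

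- Two-sided 0.05, 80% power: (1.960 × 0.7065 + 0.842 × 0.6974)² / 0.0256 = 151.9, so 152. This is the stated figure.
- One-sided 0.05, 80% power: (1.645 × 0.7065 + 0.842 × 0.6974)² / 0.0256 = 119.5, so 120.

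The loss step also holds: 2 × 152 = 304 and 304/0.85 = 357.6, which the article rounds up to 360.

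**Does 152 identify the sidedness?** The required n per group, with the unstated power and continuity correction varied:

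| Power | Two-sided 0.05 | Two-sided, corrected | One-sided 0.05 | One-sided, corrected |
|---|---|---|---|---|
| 80% | **152** | 165 | 120 | 132 |
| 85% | 174 | 186 | 139 | **152** |
| 90% | 203 | 216 | 166 | 178 |

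The one-sided match at 85% comes from n = 138.8 before correction. The corrected value is (138.8/4)·[1 + √(1 + 4/(138.8 × 0.16))]² = 151.04, so 152. One-sided 0.05 at 87.5% power without correction gives 151. Two settings therefore give 152 exactly, one of each sidedness.

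**False-superiority risk.** Nominally it is 0.05/2 = 0.025 in the direction of A&AA for a two-sided test, against 0.05 for a one-sided test. Exact binomial calculation for the pooled z test, with both true rates at 44% and 180 per group, gives 0.0247 and 0.0499.

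**Smallest significant difference.** This is z·√(2 × 0.52 × 0.48/n). With 15% loss, n = 180 × 0.85 = 153.

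| n per arm | Two-sided | One-sided |
|---|---|---|
| 153 | 1.960 × 0.0571 = 11.2 points | 1.645 × 0.0571 = 9.4 points |
| 180 | 1.960 × 0.0527 = 10.3 points | 1.645 × 0.0527 = 8.7 points |

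**Power under the assumed rates (no correction).** At 152 per arm it is 80.0% two-sided and 87.7% one-sided. At 180 per arm it is 86.3% and 92.1%.

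**Consistency with the intervals.** A 95% interval excludes zero when |z| exceeds 1.960, apart from small differences in how the standard error is formed. A one-sided 0.05 test rejects at z above 1.645. Results with z between 1.645 and 1.960 would be called significant while the 95% interval covers zero.

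**The case against.** The strongest defence has three parts.

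First, the article is condensed and an unseen analysis plan may assign sidedness test by test. That would excuse silence, but the article is not silent. It states a rule, and the rule permits both versions at the same level.

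Second, the 95% intervals point to two-sided 0.05 reporting and would make a one-sided claim easier to notice. This is true and counts in the plan's favour. It does not fix the test, however, and the intervals for the intervention effect in Handling of missing data belong to particular missing-data branches.

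Third, an independent centre is to analyse the data blinded. A reader might infer that the side of the test will be picked after the results are seen. The article does not support that inference, and the blinded analysis speaks against it. What remains is that the planned test cannot be identified from the text.

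A reader might also infer that 152 can only be a two-sided figure, so that the sample size contradicts any one-sided test. This does not hold. Power is not stated, and a one-sided calculation at 85% power with continuity correction gives the same number. Two-sided at 80% is the most natural reading but not the only one.

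**Conclusion.** The point stands as an ambiguity in a stated rule that bears on the type I error of the primary claim. Followed as written, the plan allows a one-sided 0.05 primary test with a false-superiority risk of 5% instead of 2.5%. Observed differences of about 9.4 to 11.2 points (153 per arm) or 8.7 to 10.3 points (180 per arm) would change the conclusion according to which permitted test is used.

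The thresholds assume a pooled abstinence rate of 52%. The lower n assumes that the full 15% loss occurs and that only complete cases are analysed; 180 corresponds to all randomised patients contributing an outcome. The match of 152 to a two-sided test assumes 80% power and no continuity correction. The documents do not show that the primary test will be one-sided, only that nothing in them rules it out.

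**What to change.** In Statistical analysis, replace the general sentence with a statement that the primary and other efficacy comparisons are two-sided at 0.05 with 95% confidence intervals. One-sided at 0.025 controls the same error and would serve equally. Any other one-sided test that is kept should be named, with its level.

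In Sample size, state the alpha, sidedness, power and any continuity correction actually used to obtain 152. If the calculation was two-sided 5% with 80% power, say so. The authors should report what they ran and not infer it from the match shown here.

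The cost is about one sentence in each section. The total of 360 does not change: for a two-sided uncorrected test it gives 80% power at 152 per arm and 86.3% at 180. The Discussion reports that recruitment is under way, so the change should be made and dated before outcome data are analysed.

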**Methods:**

This is a multicentre, prospective, parallel, randomized, controlled trial. A total of 360 patients with severe nicotine dependence will be randomized into test (A&AA) or control (nicotine replacement therapy, NRT) groups. The test group will be treated with A&AA twice weekly, while the control group will use an NRT patch daily. All treatments will be administered for 8 weeks, with a follow-up period of 4 months. The primary outcome will be the smoking abstinence rate at week 24, with a combined safety assessment. The secondary outcomes will be smoking cessation rates at other timepoints, saliva cortisone test results, and scores on the Fagerstrom Test for Nicotine Dependence, the Autonomy over Tobacco Scale, the Hamilton Anxiety Rating Scale, the Self-rating Anxiety Scale, and the Pittsburgh Sleep Quality Index. The cost of treatment will also be used to evaluate the economic effects of different smoking cessation interventions. Statistical analysis on the data collected from both the intention-to-treat (all randomly assigned patients) and per-protocol (patients who complete the trial without any protocol deviations) patients, will be performed using the statistical software package, IBM SPSS 27.0.

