### Elimination criteria

Patients will be eliminated from the trial based on the following criteria: (1) patients who are willing to participate, but fail to meet the inclusion criteria, and (2) those who fail to complete instructions or procedures with obvious implications for efficacy or safety.

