### Termination criteria

The trial will be terminated if the following situations occur during its course: (1) therapies exacerbate the state of the illness or lead to secondary infections; (2) external factors worsen the patients' conditions; or (3) patients are unwilling to continue the trial.

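### The ITT set for the primary outcome is tied to receiving treatment, against the abstract's all-randomised definition, and the elimination rule does not say which analysis set it affects

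*Protocol article*

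**What the plan says.** The protocol article defines the ITT set twice.

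- Abstract, Methods: "intention-to-treat (all randomly assigned patients".
- Statistical analysis: "All Subjects who will be randomized to undergo at least one treatment comprised the Intention-To-Treat (ITT) population of the study".

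The sentence after the second definition describes the safety set in nearly the same terms: "Subjects who will be randomized into groups and underwent at least one treatment constitute the Safety group of this study". The section then fixes which set carries the main result: "Primary outcome measures will be analyzed using ITT population". Secondary outcomes go to the per-protocol set, and serious protocol violators are expressly excluded from that set only.

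The Elimination criteria list two grounds for removing a patient from the trial: "patients who are willing to participate, but fail to meet the inclusion criteria", and "those who fail to complete instructions or procedures with obvious implications for efficacy or safety". No analysis set is named there. The Primary outcome section gives the denominator of the abstinence rate only as the total number of people, without saying which set that is.

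**The concern.** Whether a patient starts treatment is known only after randomisation. Blinding of patients and therapists is ruled out under Randomization and allocation, so the decision to start can depend on the arm drawn. The qualifying event also differs in kind: a first session with an acupuncturist in one arm, a first patch in the other. The Discussion expects high dropout, particularly in the treatment group. That remark concerns dropout in general, not failure to start, but it shows that the authors expect commitment to differ by arm.

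If patients who never start are mostly continuing smokers, omitting them raises the apparent abstinence rate of the arm they leave. If that is mainly the acupuncture arm, the error favours the superiority claim made in the Discussion. If it is mainly the NRT arm, it works against that claim.

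The elimination rule adds a second uncertainty. Failing to complete instructions or procedures is also mostly a post-randomisation event. Nothing says that a patient eliminated for it stays in the ITT analysis, so an analyst could apply the rule to that set.

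**Working it through.** **1. The texts side by side.** The abstract has one condition, randomisation. The Statistical analysis section adds a condition about at least one treatment. Every patient is assigned a full 8-week course, so a minimum of one treatment has no function unless it refers to treatment received. The safety definition that follows uses the same minimum. The natural reading is a modified ITT set which in practice coincides with the safety set.

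**2. The plan's own figure.** Inputs from Sample size: 44% (NRT) and 60% (A&AA), 152 per group, 15% loss, 360 in total. Power is not stated; I assume 80%, two-sided α = 0.05, with pooled variance under the null:

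n = [1.960·√(2·0.52·0.48) + 0.842·√(0.44·0.56 + 0.60·0.40)]² / 0.16² = 152 after rounding up.

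304/0.85 = 357.6, so 358 against the stated 360. The figure reproduces. The definition of the analysis set does not alter it.

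**3. Size of the possible shift.** The documents give no rate of never starting or of elimination. I assume that a share x of an arm is left out and that all those left out smoke. The arm's rate p then becomes p/(1 − x).

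| Who is left out | x = 5% | x = 10% |
|---|---|---|
| One arm at 44% | 0.44/0.95 = 46.3% (+2.3 points) | 0.44/0.90 = 48.9% (+4.9 points) |
| Both arms equally, planned difference of 16.0 points | 0.16/0.95 = 16.8 points | 0.16/0.90 = 17.8 points |

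Against the planned 16 points, the one-arm shift is 14% or 31% (2.32/16 and 4.89/16). With equal exclusion the difference moves by 0.8 or 1.8 points.

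**4. Effect on the test in the one-arm case.** Take a true rate of 44% in both arms, 180 randomised per arm, exclusions in the A&AA arm only, all smokers, and a pooled two-sided z test. With n₂ = 180(1 − x), p₂ = 0.44/(1 − x) and d = p₂ − 0.44, the rejection probability is 1 − Φ[(1.96·se₀ − d)/se₁] + Φ[(−1.96·se₀ − d)/se₁], where se₀ and se₁ are the pooled and unpooled standard errors.

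- x = 5%: about 7% instead of 5%.
- x = 10%: se₀ = 0.0540, se₁ = 0.0540, d = 0.0489, giving about 15%.

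**5. A concrete case.** NRT 79/180 and 89 quitters in the A&AA arm. Over all 180, the difference is 5.6 points and p = 0.29. With 18 A&AA non-quitters (10%) left out, 89/162 gives a difference of 11.1 points and p = 0.041. Over all 180, at least 98 quitters would be needed for p < 0.05.

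**The case against.** **The ITT sentence may only be clumsy.** It speaks of being randomised to undergo treatment, which can be read as assignment; the safety sentence speaks of patients who "randomized into groups and underwent at least one treatment constitute the Safety group", which is receipt. On that reading ITT agrees with the abstract. The ambiguity is real, so it is too strong to say that the two sets are identical by definition. But the reading leaves the one-treatment minimum without a purpose, and the sentence still needs correcting because an analyst could follow either version.

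**The elimination rule may concern the per-protocol set only.** A reader might infer that non-compliers are removed from the primary analysis. The documents do not say so: the rule names no set, and serious violators are excluded only from the per-protocol set. Its first ground can also be read as screening failure, since only eligible patients are randomised. This objection stands. What remains is that the link to the analysis sets is left open.

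**Stopping the trial.** A reader might also bring in the Termination criteria, which include the case where "patients are unwilling to continue the trial". They say nothing about analysis sets or about barring later follow-up, so they do not support the point.

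**The size is hypothetical.** This stands too. The rates, one-arm exclusion and universal smoking among those left out are all assumed. Both arms attend the clinic twice weekly, so similar exclusion in both is possible, and the shift is then small.

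**Conclusion.** The conflict between the two ITT definitions is on the face of the article and concerns the set that carries the primary result. Followed in its natural reading, the Statistical analysis definition drops never-treated patients from the primary comparison of an unblinded trial. That needs correcting before the outcome data are analysed. The elimination rule is a matter for clarification: its reach is unstated, and removal of non-compliers from ITT is an inference.

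The size cannot be estimated from the documents. Under assumed exclusion of 5% to 10%, all smokers, the shift is 2.3 to 4.9 points if it falls on one arm with a 44% rate, and 0.8 to 1.8 points in the planned difference if it falls equally on both. These are illustrations of sensitivity and do not predict the bias. The direction depends on which arm loses more patients.

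**What to change.** - **Statistical analysis:** define ITT as all randomised patients, analysed in their allocated arm whether or not treated. Keep the one-treatment condition for the safety set only.
- **Elimination criteria:** state that elimination after randomisation affects only the per-protocol set, that such patients remain in ITT, and that their week-24 outcome is sought unless they withdraw consent.
- **Handling of missing data:** state that never-treated or eliminated patients without a week-24 CO reading count in the ITT denominator and are handled as missing outcomes. Without this, the first two changes can be undone. The section permits complete-case analysis when under 5% of data are missing, or above 5% when the complete cases test as a random sample, and either route would drop the same patients again.

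The cost is wording in three sections and some continued contact with patients off treatment. Observed abstinence rates may be slightly lower. The planned 152 per group and 360 in total are unchanged.

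### Secondary efficacy outcomes are assigned to the per-protocol set with no ITT analysis beside it, so they lose the protection of randomisation, and the set for the cost analysis is left unclear

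*Protocol article*

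**What the plan says.** The Statistical analysis section assigns a set to each class of outcome. For the primary: "Primary outcome measures will be analyzed using ITT population". For the rest: "secondary outcome measures and other outcomes will be analyzed using PPS population". Safety is the one stated exception and uses the safety population.

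Entry to the per-protocol set requires that "the primary variables are clear, no baseline variables are missing", and that patients "completed all scheduled studies for the 8-week treatment period, and subjects who seriously violate the protocol will be excluded".

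The Secondary outcomes section shows what is affected: "The secondary outcomes will be the prolonged abstinence rate, the abstinence rate at other time points", then the saliva test and five scales. Safety and cost of treatment are added at the end of the same paragraph.

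Two other places bear on this:

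- The abstract (Methods) says that data from both ITT and per-protocol patients will be analysed, without tying either set to an outcome. Its definition is "per-protocol (patients who complete the trial without any protocol deviations".
- Assessment of health economics says of the cost-effectiveness analysis: "The effectiveness index will be considered the primary outcome".

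**The concern.** A known week 24 result, completion of the 8-week schedule and absence of serious violation are all settled after randomisation. They can depend on the arm and on whether the patient is managing to quit. A comparison restricted to such patients is no longer a comparison of the groups that were randomised. The authors themselves foresee dropout especially in the treatment group (Discussion, limitations), so selection may well differ by arm. If those who leave mostly smoke, the selection favours acupuncture.

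Reducing relapse is a stated aim (abstract, Background), which makes abstinence over time important. Under the plan, the rates at weeks 2 to 16 would come from the per-protocol set and the week 24 rate from the ITT population. Part of any fall between week 16 and week 24 could then come from the change of set alone.

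The restriction also works against the plan's own missing-data section, which covers secondary as well as primary outcomes. Patients with an unclear primary variable or incomplete treatment-period assessments are removed before that rule can apply.

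**Working it through.** **Inputs from the article.** Expected abstinence is 44% (NRT) and 60% (A&AA), with 152 per group, 15% loss, and 360 in total or 180 per group (Sample size). No loss by arm is given.

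**The plan's own figure.** With a pooled-variance comparison of two proportions, two-sided 0.05 and 80% power (power is not stated, so 80% is inferred):

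n = [1.960·√(2·0.52·0.48) + 0.842·√(0.44·0.56 + 0.60·0.40)]² / 0.16² = 151.9, so 152 per group.

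304/0.85 = 357.6, which the plan sets at 360. The figure reproduces. It is context only, because the point concerns the analysis set.

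**Effect of selecting completers.** Let p be the true abstinence rate in all randomised patients of an arm, d the proportion outside the per-protocol set and q the abstinence rate among those excluded. Then

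per-protocol rate = (p − d·q)/(1 − d), and its excess over p is (p − q)·d/(1 − d).

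Assume p = 0.44 in both arms (no true effect) and q = 0 (all non-completers smoke). The splits by arm are assumptions; each averages 15%.

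| Non-completion, A&AA / NRT | Per-protocol n | A&AA | NRT | Difference |
|---|---|---|---|---|
| 15% / 15% | 153 / 153 | 0.44/0.85 = 51.8% | 0.44/0.85 = 51.8% | 0 |
| 20% / 10% | 144 / 162 | 0.44/0.80 = 55.0% | 0.44/0.90 = 48.9% | +6.1 points |

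In the second row a two-sided 5% test would reject about 19% of the time with no true effect.

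**Dependence on q.** In the second row the spurious difference is (0.44 − q)·(0.20/0.80 − 0.10/0.90) = (0.44 − q)·0.139. It is 6.1 points at q = 0, 3.1 points at q = 0.22 and zero at q = 0.44. With the split reversed (10% / 20%), the sign reverses.

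**Equal loss with a true effect.** At the design rates with 15% loss in each arm and q = 0, the per-protocol rates are 0.60/0.85 = 70.6% and 0.44/0.85 = 51.8%. The difference is 18.8 points instead of 16. Equal loss is neutral only when there is no effect.

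**Change of set over time.** Suppose abstinence is a constant 44% of those randomised and loss is 15% in each arm. The per-protocol rate up to week 16 would be 51.8%, and a week 24 rate on all randomised patients would be 44.0%: an apparent fall of 7.8 points with no relapse at all.

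**Per-protocol definitions side by side.** The abstract requires completing the trial, which runs to week 24, and allows no deviation. The Statistical analysis section requires that patients "completed all scheduled studies for the 8-week treatment period" and excludes only serious violators. These select different patients.

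**Cost analysis side by side.** Its place under Secondary outcomes and the wording of "secondary outcome measures and other outcomes will be analyzed using PPS population" point to the per-protocol set. Its effect measure is the primary outcome, which is analysed in ITT. No sentence settles which set is used.

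**The case against.** The primary outcome is on ITT, so the main conclusion does not depend on the per-protocol set. That stands and limits the severity.

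The abstract promises both sets. It does not say for which outcomes, and the Statistical analysis section is the only text that assigns them, so this softens the point without curing it.

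The missing-data section allows complete-case analysis for the primary too, when less than 5% is missing or a test suggests that the complete cases are a random sample. Part of the gap between the two denominators may then disappear. This stands, and it means that copying the primary's rule to the secondaries would not secure a common denominator.

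Both arms attend twice weekly (NRT group section), so visit frequency itself does not explain different completion. This also stands; the expectation of unequal loss rests on the authors' own statement in the Discussion, which gives no figure.

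Three stronger readings are tempting but not supported:

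- A reader might infer that every outcome listed as secondary is confined to completers. Safety is listed there and is excepted.
- A reader might infer that the incremental cost-effectiveness ratio will pair costs from completers with effects from the ITT population. No passage says so. The planned bootstrapping ordinarily resamples each patient's cost and effect together, and the whole analysis could be meant on ITT. The fault is an unresolved conflict.
- A reader might take a larger bias as established. A 25% / 10% split gives 58.7% against 48.9%, or 9.8 points, but it averages 17.5% loss, above the planned 15%. The article supports no particular split.

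**Conclusion.** The point holds for secondary efficacy. As written, prolonged abstinence, abstinence at other time points and the scales are compared in a set selected after randomisation, with no ITT analysis beside it, and the abstinence rates over time rest on a different set from week 24. The two definitions of per-protocol conflict. The analysis set for cost-effectiveness is unclear.

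The size of the bias cannot be derived from the article. With no true effect, 15% overall loss and all non-completers smoking, it is zero for equal loss and 6.1 points for 20% against 10%, compared with a design difference of 16 points. It shrinks if some non-completers are abstinent. The plan should be corrected, but the defect is not critical, because the primary conclusion is not drawn from this set.

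**What to change.** Change the analysis-set wording as follows:

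- Analyse all secondary efficacy outcomes in all randomised patients as assigned. State this explicitly, because the ITT definition in the Statistical analysis section requires at least one treatment while the abstract counts everyone randomised.
- For abstinence at every time point, use one denominator of all randomised patients and count missing as smoking. Use the imputations in the missing-data section as sensitivity analyses, since counting missing as smoking penalises the arm with more dropout if some of the missing are abstinent.
- Keep the planned repeated-measures analysis for the scales, including all randomised patients with available data.
- State that both costs and effects in the cost-effectiveness analysis come from all randomised patients.
- Keep one per-protocol definition, the same in the abstract and the body, for sensitivity analysis only.

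The cost is wording. No additional patients are needed and the sample size is unchanged. Estimates may be less favourable. Because patients and therapists are unblinded and recruitment has begun, make the change before any analysis, so that the choice of set cannot appear to follow the data.
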